**STUDY PROTOCOL REC Ref: 08/H1313/1 [name]**

**Condition-specific physiotherapy for neurogenic claudication:**

**a randomised trial of older adults in a primary care based physiotherapy service**

**Background Information**

*Chronic low back pain is common in older adults:*

Chronic back pain is characteristic in older people(1), with 40% of those with back pain aged 65 or over reporting restriction in activity. Lumbar spinal stenosis is a common back condition in older patients, and the associated symptoms of neurogenic claudication can cause significant disability.

*Neurogenic claudication: a clinically meaningful subgroup of chronic low back pain:*

Neurogenic claudication (NC) is a clinical presentation offering an identifiable subgroup of low back pain patients. The terms lumbar spinal stenosis (LSS) and neurogenic claudication are often used interchangeably, although NC is a clinical syndrome and LSS is a pathoanatomical finding referring to narrowing of the spinal or nerve root canals and diagnosed by CT or MRI imaging. Narrowing can be caused by age-related degeneration(2), but as LSS is not always symptomatic(3) the term 'spinal stenosis' may have little clinical meaning(4). In the non-surgical setting, the syndrome of NC provides a recognisable and meaningful clinical subgroup of chronic low back pain patients, defined by posture-related symptoms without the need for expensive spinal imaging.

*What is known about Neurogenic Claudication?*

NC has been described as 'poorly localized pain, paraesthesiae and cramping of the lower extremities of a neurologic origin'(5). Onset of NC symptoms is usually insidious, developing over time following a history of chronic low back pain. These symptoms are posture-related, associated with walking and standing(2), when the cauda equina/lumbosacral nerve roots and their blood supply are compressed(5,6,7,8) and walking tolerance can become severely limited(5,9,10,11).

*Current management of Neurogenic Claudication:*

There are no data on treating NC as a clinical syndrome without the additional use of diagnostic imaging to confirm the presence of LSS. This is despite acknowledgement in the literature that imaging findings are costly to acquire and correlate poorly with clinical presentation(4). Thus, there is a substantial literature related to the management of LSS, rather than NC, and this mostly examines surgical therapies.

Surgical treatment aims to alleviate compression on the neural tissues. There is, however, 'considerable variation in long-term benefit from surgical decompression'(6), and a recent Cochrane review concludes that data on indications for surgery and predictors of surgical outcome are lacking(12). Surgery is not, therefore, always the treatment of choice for patients with LSS-related NC. Non-surgical interventions, including physiotherapy are recommended almost universally for initial treatment(6,13,14,15). However, there is no consensus on what this non-surgical treatment should be.

Physiotherapy: There is evidence to support the use of exercise therapy for chronic back pain conditions in general(16/17), but it is increasingly recognised that research is required to investigate specific treatments and exercise programmes for defined subgroups of low back pain(18,19,20). The few non-RCT studies of exercise therapy for patients with LSS and NC(21-25) suggest that condition-specific exercises may be beneficial. A thorough review of the literature, however, has revealed no randomised trials evaluating the effectiveness of specific exercise therapy for NC compared to natural history.

*Why conduct this trial in Leeds?*

The Leeds Musculoskeletal (MSK) Service is a city-wide, primary-care run service which sees 28,000 referrals per year. A recent audit indicated that one third of referrals were for spinal problems, of which three quarters were lumbar spine problems. The MSK service has close links with the Leeds neurosurgical service which provides a tertiary spinal surgery service to the population of Yorkshire with least 8 patients per month listed for surgery for LSS.

The proposed principal investigator holds both a clinical NHS contract with the Leeds PCT and a University academic contract. The collaboration between the primary care MSK service and experienced trialists within the Academic Unit of Musculoskeletal Disease will combine extensive clinical experience with expertise in clinical trial design and analysis. The collaboration will also help develop further the clinical research culture among allied health professionals working in the NHS team.

**Summary of Background**

NC is a common, clinically-definable subset of older low back pain patients, which does not require MRI for diagnosis. Physiotherapy is generally recommended as first line therapy, but clinical trial evidence to support this recommendation is lacking. Given the posture-dependent nature of NC symptoms, we hypothesise that a rehabilitation program focussed on posture would be a rational intervention. The conservative management of NC has been identified as a research priority need by the Agency for Healthcare Research and Quality(13).

**Aims and purpose of the proposed research**

The aim of the study is to establish the effectiveness of an exercise programme aimed at addressing the specific posture-related symptoms of this condition. The purpose of the trial is to investigate the null hypothesis that a tailored exercise programme is no more effective than simple advice in improving symptoms and function in older patients with neurogenic claudication.

*Primary objective*

■ To investigate whether a condition-orientated physiotherapy exercise programme is more effective than education and advice in reducing pain and disability in the short-term.

*Secondary objectives*

■ To assess changes in subjectively reported disability and general health status

■ To investigate changes in objective measurements of walking tolerance

■ To ascertain if any improvement in either group is maintained at 12 month follow-up

■ To assess further healthcare use during a 12 month follow-up period

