**Trial procedure**

This is a single blind pragmatic randomised controlled trial. Both the intervention group and the control group will receive educational information and advice. Subjects randomised to receive the active physiotherapy intervention in addition to advice will be taught a rehabilitation programme tailored to address the posture-related pain and dysfunction associated with neurogenic claudication.

*Outcome Measurement*

Primary outcome measures will consist of score changes in the symptom severity scale of the Swiss Spinal Stenosis (SSS) questionnaire to be measured at 8 week follow-up assessment. The SSS has been been used since the early 1990s, and was specifically designed for the evaluation of patients with symptoms associated with lumbar spinal stenosis. It has been shown to be a reliable and valid outcome measure for this patient group(26).

Secondary outcome measures will include the Oswestry Disability Index (a commonly used measure of pain and function in low back pain), the General Well-being Index (providing a quality of life measure), objective measurement of walking tolerance (shuttle walking test), and 12 month Swiss Spinal Stenosis score.

*Sample size*

This study will be powered to detect a 0.5 point difference in the primary outcome measure; the Swiss Spinal Stenosis questionnaire symptom severity scale: The Minimum Clinically Important Difference for scores in this measure has been determined previously as a change of at least 0.5 points in the symptom severity scale and in the physical function scale (27). Population standard deviations of samples reported in previous studies (28,29) range from 0.48 to 0.56; and the more conservative figure of 0.56 has been adopted for powering this study.

The proposed sample size is based on the ability to detect a difference (Δ) in treatment groups of 0.5 points in the symptom severity scale, with a standard deviation of 0.56, and based on a power of 90% (alpha 5%). The required sample size at exit is 28 subjects and 28 controls. To allow for group size differences due to randomisation, and for a drop-out rate of 20%, a total recruitment of 76 patients is planned.

*Subject Recruitment*

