**Physiotherapy exercise programme**

Each patient randomised to this group will be taught a programme of exercises by the treating physiotherapist, selected from a list of possible exercises (see below)and will be instructed to perform the selected programme of exercises twice daily. These exercises are based on flexion movements and postural adaptation to reduce symptoms from neural compression and include exercises improve fitness. The treating physiotherapist will review each subject at least 4 times and up to six times during the 6 week treatment period and will guide each subject in progressing the exercises (intensity, duration or repetitions) as appropriate. The physiotherapist will encourage compliance during treatment and encourage continuation of the exercise programme after the treatment period. In order to standardise the physiotherapy rehabilitation programme, a training session for physiotherapists administering interventions will be held by the study co-ordinator prior to commencement of the study.

*Follow-up*

All outcome measures will be repeated at 8 weeks and questionnaire outcomes will be repeated at 12 months from randomisation. These measures will be administered by the study co-ordinator who will be blinded to the intervention received.

All clinical assessment and treatment sessions will be administered in primary care outpatient clinics most convenient to the study participants.

*Dropouts and anticipated problems with compliance*

Problems with compliance and participant dropout from the trial are expected to be minimal due to the nature of the interventions and relatively short trial period. For genuine dropouts, every effort will be made to retrieve exit data for the primary endpoint, which may include telephone follow-up. The intention-to-treat approach to the analysis of this pragmatic trial designs ensures that compliance failures in both treatment arms will contribute valid data to the evaluation.

*Statistical Analysis*

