The Academic Unit employs a statistician who has input into preparation of this application and who will work with the study team during the analysis phase. Descriptive exploration will compare the pre and post intervention data for the two groups, exploring for change in Swiss Spinal Stenosis (SSS) symptom severity and physical function scores. Inferential analysis of the pre-and post-intervention SSS symptom severity data will be based on multi-variable models appropriate to the data type, including baseline data as covariates (ANCOVA). The primary analysis will be undertaken according to intention to treat principles, with missing data excluded. A secondary analysis will also be performed where missing data will be analysed assuming worst-case values.

*Study timetable*

The study will have a 3 month run-in period, and will allow 18 months for recruitment.

Following 12 month follow-up, a further 3 months will be allowed for data cleansing, analysis, and preparation of the final report by the end of the three year trial period.

*Trial Management*

A trial steering committee, with an independent chair and lay representation will be set-up within the Leeds Academic Unit of Musculoskeletal Disease. The trial steering committee will receive 3-monthly reports from the study co-ordinator regarding recruitment and trial progress and will be responsible for external reporting to the funder and regulatory authorities. This committee, in conjunction with the Academic Unit's standing data-monitoring committee (chaired by [name]) will monitor adverse event management and all data-related aspects of the management of the trial. Day to day trial management will be overseen by a trial management group comprising the grant holders, the department's business manager and trial staff.

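### The 12-month objective asks whether improvement lasts within each group; it should ask whether the randomised groups differ at 12 months

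*Protocol*

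**What the plan says.** Under Aims and purpose, the primary objective is comparative but limited to the short term: whether the exercise programme "is more effective than education and advice in reducing pain and disability in the short-term". The secondary objective on durability is worded differently: "To ascertain if any improvement in either group is maintained at 12 month follow-up". It names no comparator and takes improvement as its starting point.

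Three other places bear on the 12-month question:

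- The null hypothesis, in the same section, is between groups and has no time limit: "a tailored exercise programme is no more effective than simple advice in improving symptoms and function in older patients with neurogenic claudication".
- Outcome Measurement ends its list of secondary outcomes with "objective measurement of walking tolerance (shuttle walking test), and 12 month Swiss Spinal Stenosis score". It attaches no contrast to the 12-month score.
- Follow-up provides for the data: "All outcome measures will be repeated at 8 weeks and questionnaire outcomes will be repeated at 12 months from randomisation", administered by a blinded co-ordinator.

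Statistical Analysis first describes an exploratory step: "Descriptive exploration will compare the pre and post intervention data for the two groups". It then gives the inferential method: "Inferential analysis of the pre-and post-intervention SSS symptom severity data will be based on multi-variable models appropriate to the data type", with baseline data as covariates. Neither sentence mentions 12 months.

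**The concern.** An analysis plan takes its questions from the protocol's objectives. One that followed this objective literally would test, in the exercise arm and then in the advice arm, whether the change from baseline is still present at 12 months, and would report two answers.

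There are two difficulties. First, change within an arm mixes the effect of treatment with natural course, symptom fluctuation and any regression to the mean. The protocol's own background gives the lack of randomised evidence against natural history as a reason for the trial, so this is the distinction the trial is meant to draw. Second, two within-arm results invite the reader to compare them. Maintained with exercise but not with advice sounds like a treatment effect, yet it can arise readily when the arms do not differ. Conversely, if both arms are reported as maintained, a real difference between them can go unremarked.

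**Working it through.** **The protocol's own figure.** The inputs are a difference of 0.5, SD 0.56, power 90% and alpha 5% (Sample size). Two-sided, by the normal approximation:

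n per arm = 2 × (1.960 + 1.282)² × 0.56² / 0.5² = 2 × 10.51 × 1.254 = 26.4, rounded up to 27.

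The two-sample t-test gives 27.4, rounded up to 28, with power 0.907 at 28. The stated 28 per group is reproduced. It applies to the 8-week comparison and is not disputed; 28 per arm and SD 0.56 are carried forward below.

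**How often two within-arm tests disagree when the arms are the same.** Inputs:

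- SD 0.56 and 28 per arm, from the protocol. 28 is the planned number at exit; fewer may remain at 12 months.
- Correlation r between baseline and 12 months of 0.5 to 0.7. This is assumed, as the protocol gives none.
- True improvement at 12 months of 0.2 points in both arms. This is assumed, with no difference between arms.
- A paired t-test in each arm, two-sided 5%, critical value 2.052 on 27 degrees of freedom.

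Formulas: SD of change = 0.56 × √(2(1 − r)); standard error = SD of change / √28; non-centrality = 0.2 / standard error; p = power of the paired t-test. The arms are independent, so the chance that exactly one is significant is 2p(1 − p).

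| r | SD of change | SE | Non-centrality | p | 2p(1 − p) |
|---|---|---|---|---|---|
| 0.5 | 0.560 | 0.106 | 1.89 | 0.445 | 0.494 |
| 0.6 | 0.501 | 0.095 | 2.11 | 0.531 | 0.498 |
| 0.7 | 0.434 | 0.082 | 2.44 | 0.653 | 0.453 |

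The two arms therefore give different answers in about 45-50% of trials. By symmetry, half of these (23-25% of trials) favour exercise and half favour advice.

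**Sensitivity to the assumed 0.2.** 2p(1 − p) cannot exceed 50%, which it reaches when p = 0.5, so 0.2 lies close to the worst case. Over the same range of r:

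| Common true improvement | Chance that exactly one arm is significant |
|---|---|
| 0.1 | 25-34% |
| 0.2 | 45-50% |
| 0.3 | 11-34% |
| 0.5 | 1% or less |

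A test of the difference between arms would show a significant difference in about 5% of trials in every one of these cases, because the arms are equal.

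**Regression to the mean from baseline.** Suppose entry were effectively restricted to patients above a cut-off of −0.5 to +0.5 SD on the SSS, with r from 0.5 to 0.8 (all assumed). The expected spurious improvement is (1 − r) × 0.56 × λ, where λ is the mean of a standard normal truncated at the cut-off. This gives 0.06 to 0.32 points. With no selection on severity it is 0. The expected shift is the same in both randomised arms, so it cancels from the difference between them but not from either within-arm change.

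**The case against.** The strongest reply is that the protocol already contains what is asked for. The null hypothesis is between groups with no time limit, the listed secondary outcome is "and 12 month Swiss Spinal Stenosis score" without any condition on earlier response, and the score is collected in both arms from randomisation. The planned ANCOVA extends naturally to 12 months, and the model for a secondary time point may properly sit in an analysis plan that is not shown. Whether response lasts is also a legitimate descriptive question.

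Much of this stands. A reader might infer that the plan throws away the randomised comparison at 12 months; nothing in the text says so, and the outcome list and follow-up schedule point the other way. Nor is this the only objective that could reach 12 months, since the one on disability and general health status carries no time limit.

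A reader might also infer that regression to the mean is bound to distort the 12-month result. The documents do not support that. There is no SSS threshold for entry; required functional limitation makes some regression plausible, but its size cannot be derived.

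It is tempting, too, to take patients who improved at 8 weeks and show that they fall back by chance. But the objective speaks of groups, and no responder subset is planned. At arm level the effect is small. With no true change and equal correlations of 0.5 to 0.7 between visits, an arm selected because its mean improved at all has an expected 8-week change of SE × √(2/π) = 0.065 to 0.084 points. Half of this, 0.03 to 0.04 points, is lost by 12 months.

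What the reply does not meet is the wording itself. The missing model can be left to an analysis plan; the question that the model must answer is set by the objective, and here that question is within group.

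**Conclusion.** The point holds as a fault in the wording of a secondary objective. As written, the 12-month objective leads to a verdict for each arm, and two such verdicts cannot support a conclusion about treatment. With equal arms they would disagree in about 45-50% of trials if the common retained improvement were 0.2 points. This rests on the protocol's SD and exit numbers, an assumed correlation of 0.5 to 0.7, and significance of a paired test as the criterion for maintenance. The figure is near its maximum at 0.2 and falls to 1% or less at 0.5, so it shows how large the problem can be and is not a prediction. That a contrast of two within-arm results is not a test between arms does not depend on these assumptions.

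The between-arm comparison is omitted from the objective, not excluded by the protocol. The primary 8-week comparison and its sample size are unaffected.

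**What to change.** Reword the objective along these lines: to estimate the difference between groups in SSS symptom severity at 12 months, adjusted for baseline, in all randomised patients with 12-month data. Under Statistical Analysis, state that the planned ANCOVA is also applied at 12 months, with the estimate and its 95% confidence interval. A repeated-measures model covering 8 weeks and 12 months would serve equally well, and that choice can be left to the analysis plan. Keep maintenance within each arm, if wanted, as description without tests.

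The cost is one reworded sentence and one additional model. No new data are needed, because the questionnaires are already scheduled in both arms at 12 months.

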**Trial procedure**

This is a single blind pragmatic randomised controlled trial. Both the intervention group and the control group will receive educational information and advice. Subjects randomised to receive the active physiotherapy intervention in addition to advice will be taught a rehabilitation programme tailored to address the posture-related pain and dysfunction associated with neurogenic claudication.

*Outcome Measurement*

Primary outcome measures will consist of score changes in the symptom severity scale of the Swiss Spinal Stenosis (SSS) questionnaire to be measured at 8 week follow-up assessment. The SSS has been been used since the early 1990s, and was specifically designed for the evaluation of patients with symptoms associated with lumbar spinal stenosis. It has been shown to be a reliable and valid outcome measure for this patient group(26).

Secondary outcome measures will include the Oswestry Disability Index (a commonly used measure of pain and function in low back pain), the General Well-being Index (providing a quality of life measure), objective measurement of walking tolerance (shuttle walking test), and 12 month Swiss Spinal Stenosis score.

*Sample size*

This study will be powered to detect a 0.5 point difference in the primary outcome measure; the Swiss Spinal Stenosis questionnaire symptom severity scale: The Minimum Clinically Important Difference for scores in this measure has been determined previously as a change of at least 0.5 points in the symptom severity scale and in the physical function scale (27). Population standard deviations of samples reported in previous studies (28,29) range from 0.48 to 0.56; and the more conservative figure of 0.56 has been adopted for powering this study.

The proposed sample size is based on the ability to detect a difference (Δ) in treatment groups of 0.5 points in the symptom severity scale, with a standard deviation of 0.56, and based on a power of 90% (alpha 5%). The required sample size at exit is 28 subjects and 28 controls. To allow for group size differences due to randomisation, and for a drop-out rate of 20%, a total recruitment of 76 patients is planned.

*Subject Recruitment*

Subjects will be recruited from patient referrals to the Leeds primary care Musculoskeletal service or Neurosurgical service. The Leeds Musculoskeletal (MSK) Service is a city-wide, primary-care run service which sees approximately 28000 referrals per year. A recent audit of the primary care MSK service reported that almost one third of referrals were for spinal problems, of which three quarters were lumbar spine problems. The number of lumbar spine referrals over the recruitment time of 18 months can therefore be conservatively estimated to be approximately 10,400. Using previously published prevalence figures which suggest that 3-4% patients with low back pain are older patients with lumbar spinal stenosis, and based on a conservative 50% prevalence of neurogenic claudication amongst this group, approximately 200 referrals for patients with neurogenic claudication over 18 months through the primary care MSK service can be estimated. In addition, patients with neurogenic claudication will be recruited from referrals to the Leeds neurosurgical service which provides a tertiary spinal surgery service to the population of Yorkshire and where currently at least 8 patients per month are listed for surgery for LSS.

Potentially eligible patients will be sent a study information leaflet providing details of the aims of the study and what participation in the trial will involve. Subjects will subsequently be contacted by telephone for initial screening and to ascertain willingness to participate. Interested eligible subjects will then attend a clinic appointment for final screening for inclusion and exclusion criteria. Eligible subjects who are willing to participate will be recruited by the study co-ordinator after informed consent has been gained.

Inclusion criteria

1. Age 50 years or older with symptoms of NC, defined as bilateral non-dermatomal lower limb symptoms (below the gluteal fold), induced on erect walking and eased in sitting or flexion of the lumbar spine. Lower limb symptoms may include pain, heaviness, aching, cramping, paraesthesia, or weakness.

2. Limitation of normal walking tolerance or function due to symptoms of neurogenic claudication

Exclusion criteria will include subjects with clearly defined radicular symptoms (sciatica), cognitive impairment or medical conditions preventing understanding or participation in the study, and subjects with symptoms requiring urgent surgical or other intervention (red flags – see below).

Red Flags (CSAG 1994) – Indicators of potential serious pathology

■ Age of onset <20 or > 55 years

■ Violent trauma, eg fall from a height, road traffic accident

■ Constant progressive, non-mechanical pain

■ Thoracic pain

■ Past medical history of carcinoma

■ Systemic steroids

■ Drug abuse, HIV

■ Systemically unwell

■ Weight loss

■ Persistent severe restriction of lumbar flexion

■ Widespread neurology

■ Structural deformity

*Randomisation*

Treatment will be determined by simple block randomisation. Web-based randomisation will occur after written informed consent and baseline measures have been obtained and will be based on a computer-generated randomisation protocol.

*Study plan*

Following recruitment to the study, participants will be randomised either to the advice only intervention, or to the advice plus active physiotherapy rehabilitation intervention. It will not be possible to blind subjects to the treatment they receive, and it is recognised that outcome is possibly influenced by preconceived ideas regarding the effectiveness of intervention(30,31). Subjects' treatment preferences will therefore be elicited prior to randomisation, so that this information may be used to inform the analysis of outcomes.

